### Recruitment

School recruitment commenced in September 2022 and will continue until December 2023. A study advertisement has been emailed to all schools in the sampling frame. Following our propensity sampling approach, schools are then invited by post and email with a telephone follow-up. In participating schools, a School Liaison Member (SLM) of staff is identified and a school–university contract outlining expected commitments signed. Subsequently, a member of SLT responsible for the smartphone policy, and pupils and teachers from the year 8 and year 10 classes are recruited. £600 compensation is allocated to each school and a £5 voucher per pupil participant.

Parents/carers are provided with written detailed information about the study, what their child’s participation will involve and how their child’s data will be processed. Schools are asked to assist in the distribution of this information to parents/carers in different formats (eg, email, post, text messages, website, and so on).

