### Sampling and participants

To improve the comparability of the two school groups, stratified sampling based on propensity scores was employed.^57^ We obtained routine data from the Department for Education on the following school characteristics: region, school type, urban or rural, total pupil roll size, Income Deprivation Affecting Children Index (IDACI),^58^ inclusion of a sixth form, selective or non-selective admissions policy, religious affiliation and the proportion of pupils with the following characteristics: male, from BAME groups, English as an additional language, eligible for free school meals and special education needs. Propensity scores were calculated using restrictive or permissive school smartphone policies as the outcome and school characteristics as explanatory variables. Propensity score terciles were then used to create three groups with subsequent division by restrictive or permissive policy type, resulting in six distinct sampling groups. Schools in each group have been randomly ordered and are being invited sequentially to participate, aiming to recruit six to seven schools from each restrictive tercile and three to four from each permissive tercile to achieve a sample size of 20 schools with restrictive and 10 schools with permissive policies.

In participating schools, two classes of mixed ability year 8 (age 12–13) and year 10 (age 14–15) pupils are recruited. We are focusing on adolescents in this age range because of the age of onset and prevalence of mental illness,^5^ and the prevalence of smartphone and social media use by adolescents aged 12–15.^7 14 59^ Within this age range we may also be able to observe potential differences in smartphone/social media use relationships with well-being.^33^ For example, year 8 pupils are likely to be newer users of phones/media and physical activity levels begin to decline at this age, particularly among girls.^7 13^ In year 10, pupils are more likely to be established phone/media users, mental well-being tends to be lower, and this age group are approaching the peak onset of mental health conditions.^4^ In addition to adolescent participants, the form teacher for each class recruited (or an equivalent teacher responsible for the class) and a member of senior leadership team (SLT) who is responsible for the school smartphone policy are recruited from each school.

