### Sample size calculation

To account for the imbalance of schools in our sample that have permissive (n=125) and restrictive policies (n=1220), we are recruiting schools using a 2:1 (restrictive: permissive) ratio. The primary outcome of mental well-being will be measured using the Warwick-Edinburgh Mental Well-Being Scale (WEMWBS; score range=14–70).^60^ To detect a mean difference in score of three points (considered the minimum clinically important difference^60^ between the two school groups), assuming a SD of 6.8^61^ and an ICC of 0.1 (a conservative estimate^62^), with 90% power and 5% significance, we require 20 schools in the restrictive and 10 schools in the permissive smartphone policy groups, with an average cluster size of 39 (1170 pupil participants in total; 780 in the restrictive, and 390 in the permissive policy groups).

In each participating class, we aim to recruit a minimum of 19–20 pupils (67% if estimated class size n=30). In studies with multiple layers of clustering (here classes within schools), it is conservative to treat clusters within clusters as one larger cluster, which is the approach used here.^63^

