### Data collection

Data collection methods include self-administered surveys for pupils, teachers and a member of the SLT; accelerometer measured physical activity and sleep for pupils; and document analysis. All online surveys are completed using university-approved online survey software (REDCap). Table 3 provides an overview of outcomes, measures and timepoints of evaluation.

**Table 3 T3:** Overview of outcomes, measures and timepoints of evaluation

Outcome	Outcome measures	Timepoint(s) of evaluation
Primary outcome		
Mental well-being	Warwick-Edinburgh Mental Well-Being Scale (WEMWBS)^60^/pupil survey	Measured over the past 2 weeks at two time points, 4–8 weeks apart
Secondary outcomes		
Anxiety symptoms	Generalised Anxiety Disorder Assessment (GAD-7)^77^/pupil survey	One time point measured over the past 2 weeks
Depressive symptoms	Patient Health Questionnaire (PHQ-9)^78^/pupil survey	One time point measured over the past 2 weeks
Addictive use	Problematic Social Media use Scale^49 50^/pupil survey	One time point based on usual use
Sleep	Sleep quality (indicated by sleep duration and sleep efficiency/accelerometers) Time pupils go to sleep and wake time on a school day and a weekend day/pupil survey	Over 7 days/usual behaviours
Physical activity	Physical activity (total and moderate-to-vigorous intensity (MVPA)/accelerometers) Active travel and sports/activity club engagement/ pupil survey	Over 7 days/usual behaviours Usual behaviours
Attainment	Assessment of whether pupils are below, above or working at their target grade in English and Maths/teacher survey	One time point—most recent assessment
Disruptive classroom behaviour	Pupil Behaviour Questionnaire^79^/teacher survey	One time point—current assessment
Intermediate outcomes		
Smartphone use duration	3 measures: (i) within school; (ii) over 24-hour period on a school day; (iii) on a weekend day/data captured from iOS and Android smartphones and will be self-reported through the pupil survey	One time point
Social media use duration	3 measures: (i) within school; (ii) over 24-hour period on a school day; (iii) on a weekend day/data captured from iOS and Android smartphones and will be self-reported through the pupil survey	One time point
Motives for social media use	Social Media Motives Questionnaire/pupil survey	One time point measured over past 12 months
Policy implementation measures		

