### Data analysis

#### Analysis of pupil outcomes

The primary analysis will examine the association between pupil mental well-being and school policy type (restrictive/permissive). Multilevel linear models will be developed, accounting for repeated measures, clustering of classes and schools and adjusting for the school-level variables included in the propensity score estimations alongside relevant individual-level sociodemographic variables. Secondary analyses will use the same modelling approach investigating differences in the secondary (behavioural and mental health) and intermediary (smartphone and social media use) outcomes between school policy groups. Differential association between school policy and the primary, secondary and intermediary outcomes will also be explored across: (1) socioeconomic position; (2) gender; and (3) ethnicity by including relevant interaction terms in the developed models.

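### Time of year is close to a school-level factor for accelerometer activity and sleep, and neither the sampling nor the stated adjustment set accounts for it; one prespecified seasonal covariate would be a cheap improvement

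*Protocol article*

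**What the plan says.** Under Recruitment, the protocol article states: "School recruitment commenced in September 2022 and will continue until December 2023". The opening of Methods and analysis gives the study period as April 2022 to July 2024. Dates of data collection are not given.

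Under Sampling and participants, schools are divided by propensity-score tercile and policy type into six groups. "Schools in each group have been randomly ordered and are being invited sequentially to participate". The propensity score uses 13 school characteristics, none of them a calendar variable. Study setting gives the pools as 1220 restrictive and 125 permissive schools.

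The main pupil survey is done once, and the accelerometer is worn for the 7 days that follow it. Table 3 gives the timing of the sleep and physical activity outcomes as "Over 7 days/usual behaviours". WEMWBS alone is repeated, 4 to 8 weeks later.

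Under Analysis of pupil outcomes, the multilevel models account for repeated measures and for class and school clustering, "adjusting for the school-level variables included in the propensity score estimations alongside relevant individual-level sociodemographic variables". Term, month and season of measurement are not mentioned.

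**The concern.** Activity and sleep plausibly vary with daylight and weather. When a school contributes one accelerometer week, all or nearly all of its pupils are measured at the same time of year, and season cannot be separated from school. With 20 schools against 10, the policy groups may differ appreciably in when they were measured.

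Propensity-score sampling cannot deal with this, because the measurement date arises after the school has been sampled. Random ordering within each of the six groups settles who is approached first inside a group. It does not make restrictive and permissive schools fall in the same term. If the two groups fill at different speeds, part of a seasonal difference would appear as a policy effect. The stake is mainly in accelerometer-measured activity and sleep. WEMWBS is exposed too, because two readings 4 to 8 weeks apart lie in the same or adjacent seasons, but the likely effect there is small.

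**Working it through.** **1. The plan's own sample size.** Inputs from Sample size calculation: a 3-point difference, SD 6.8, ICC 0.1, "with 90% power and 5% significance" (taken as two-sided), ratio 2:1, 39 pupils per school.

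- Unclustered permissive group: 1.5 × 6.8² × (1.960 + 1.282)² / 3² = 80.98.
- Design effect: 1 + (39 − 1) × 0.1 = 4.8.
- Permissive pupils: 80.98 × 4.8 = 388.7, or 9.97 schools of 39, so 10 schools. With 20 restrictive schools the total is 30 × 39 = 1170. The stated figure reproduces, and this point does not affect it.
- Standard error of the policy difference: 6.8 × √[4.8 × (1/390 + 1/780)] = 0.924. Power by normal approximation is 90.1%.

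**2. Chance imbalance in timing.** Assume that schools fall independently and with equal probability into two half-years.

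- SD of the difference in shares: √(0.25/20 + 0.25/10) = 0.194.
- Exact binomials: P(gap ≥ 20 points) = 0.369; P(gap ≥ 30 points) = 0.156.
- If exactly 15 of the 30 schools fall in each half (hypergeometric): P(gap ≥ 30 points) = 0.245.

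These figures describe chance. The expected gap is zero, so they do not show bias.

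**3. Season as noise in WEMWBS.** Between-school variance under the plan: 0.1 × 6.8² = 4.62. A swing of s points over two equal halves has variance s²/4. For an assumed s of 1 to 2 this is 0.25 to 1.0, or 5% to 22% of 4.62. In the policy difference it is (1/20 + 1/10) × 0.25 to 1.0 = 0.04 to 0.15, against a total variance of 0.924² = 0.85. It may already lie inside the assumed ICC.

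**4. Season as confounder.** The shift in the policy estimate is gap × swing. At a gap of 30 points, with swings that are assumptions because the article gives none:

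| Outcome | Assumed swing | Shift |
|---|---|---|
| MVPA | 5 / 10 / 15 min/day | 1.5 / 3.0 / 4.5 min/day |
| WEMWBS | 1 / 2 points | 0.3 / 0.6 points |

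If that gap were systematic, the false-positive rate for WEMWBS, 1 − Φ(1.96 − b/0.924) + Φ(−1.96 − b/0.924), would be 6.2% at b = 0.3 and 10.0% at b = 0.6. No target difference or SD is given for activity or sleep, so the MVPA shifts cannot be scaled in the same way.

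**5. Cost of one season term,** on the WEMWBS inputs. With two-thirds of schools restrictive and a half-and-half season split, the squared correlation of policy and season is gap² × (2/9)/0.25, and the variance factor is 1/(1 − that value).

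- Gap 0: factor 1.00, power about 90%.
- Gap 30 points: 1/(1 − 0.08) = 1.09, power about 88%.
- Gap 60 points: 1/(1 − 0.32) = 1.47, power about 76%.

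These are normal approximations. They ignore any between-school variance that season explains, which would offset some of the loss, and they ignore the degrees of freedom used by other covariates.

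**The case against.** The strongest reply is that chance imbalance is not bias. If visit timing is unrelated to policy, the expected distortion is zero and the seasonal component is school-level variation, which the planned clustering by school carries into the standard error. That stands, and the probabilities in step 2 should not be read as probabilities of a biased result.

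A reader might infer from the pools of 1220 and 125 that permissive schools are recruited later. The article does not support this. The permissive target is also smaller (10 against 20), every group is invited sequentially in random order, the advertisement went to all schools in the frame, and nothing says that one policy group goes first. Different pace is a possibility that the design does not exclude, and no more than that.

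A third reply is that a condensed article leaves visit scheduling and final covariates to the full protocol or the analysis plan, which are not shown. This stands in part: the models are still to be developed, and a seasonal term may be written elsewhere. But the article does more than stay silent. It names the adjustment set as the propensity variables plus sociodemographics, and time of measurement belongs to neither.

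Finally, the model is already heavily loaded. With 30 schools, an intercept, policy and 13 school characteristics at one coefficient each, at most 30 − 1 − 1 − 13 = 15 school-level degrees of freedom remain, and fewer once region and school type take several each. That is a fair reason to limit any addition to one term.

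**Conclusion.** The point holds as a modest, inexpensive improvement, chiefly for accelerometer activity and sleep. Recruitment rolls over about 16 months, each school's activity and sleep rest on one 7-day window, no stated step aligns calendar time between policy groups, and the stated adjustment set has no calendar term. Season therefore can confound the comparison if pace differs by policy; otherwise it adds noise.

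Two stronger conclusions might be drawn, and the article supports neither. One is that season does bias the policy estimates: no visit dates are given, and no difference in pace is shown. The other is that the primary analysis is in serious doubt: under an assumed swing of 1 to 2 points and a 30-point gap, the WEMWBS shift is 0.3 to 0.6, below the standard error of 0.92 and at most a fifth of the 3-point target (0.6/3).

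The conclusion rests on assumed seasonal swings, a two-half-year simplification, and the inference that a school's pupils are measured at about the same time.

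**What to change.** In Analysis of pupil outcomes:

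1. Add one prespecified seasonal covariate, daylight hours computed from the recorded wear dates, to the models for accelerometer activity and sleep.
2. Report term of measurement by policy group beside the school characteristics.
3. For WEMWBS, keep the primary model as it is and add term of measurement as a sensitivity analysis only.
4. Where visits remain to be booked, aim for about two restrictive schools per permissive school in each term.

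The cost is some visit scheduling and one school-level degree of freedom in a 30-school model that already adjusts for 13 school characteristics. The power loss is near zero if season is balanced and small at a 30-point imbalance (about 90% to 88% on the WEMWBS inputs). It would be material at 60 points (about 76%), which is a further reason to balance the remaining visits. Prespecifying the term also avoids choosing it after the data are seen. If recruitment has already closed, items 1 to 3 remain possible.

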### Data collection

Data collection methods include self-administered surveys for pupils, teachers and a member of the SLT; accelerometer measured physical activity and sleep for pupils; and document analysis. All online surveys are completed using university-approved online survey software (REDCap). Table 3 provides an overview of outcomes, measures and timepoints of evaluation.

**Table 3 T3:** Overview of outcomes, measures and timepoints of evaluation

Outcome	Outcome measures	Timepoint(s) of evaluation
Primary outcome		
Mental well-being	Warwick-Edinburgh Mental Well-Being Scale (WEMWBS)^60^/pupil survey	Measured over the past 2 weeks at two time points, 4–8 weeks apart
Secondary outcomes		
Anxiety symptoms	Generalised Anxiety Disorder Assessment (GAD-7)^77^/pupil survey	One time point measured over the past 2 weeks
Depressive symptoms	Patient Health Questionnaire (PHQ-9)^78^/pupil survey	One time point measured over the past 2 weeks
Addictive use	Problematic Social Media use Scale^49 50^/pupil survey	One time point based on usual use
Sleep	Sleep quality (indicated by sleep duration and sleep efficiency/accelerometers) Time pupils go to sleep and wake time on a school day and a weekend day/pupil survey	Over 7 days/usual behaviours
Physical activity	Physical activity (total and moderate-to-vigorous intensity (MVPA)/accelerometers) Active travel and sports/activity club engagement/ pupil survey	Over 7 days/usual behaviours Usual behaviours
Attainment	Assessment of whether pupils are below, above or working at their target grade in English and Maths/teacher survey	One time point—most recent assessment
Disruptive classroom behaviour	Pupil Behaviour Questionnaire^79^/teacher survey	One time point—current assessment
Intermediate outcomes		
Smartphone use duration	3 measures: (i) within school; (ii) over 24-hour period on a school day; (iii) on a weekend day/data captured from iOS and Android smartphones and will be self-reported through the pupil survey	One time point
Social media use duration	3 measures: (i) within school; (ii) over 24-hour period on a school day; (iii) on a weekend day/data captured from iOS and Android smartphones and will be self-reported through the pupil survey	One time point
Motives for social media use	Social Media Motives Questionnaire/pupil survey	One time point measured over past 12 months
Policy implementation measures		
Intervention components (school level data): school timetable; school policies (smartphone, mental health, behaviour, e-safety): school smartphone policy details (eg, rules/key features; time period of implementation; policy communication and understanding; adherence and fidelity and policy rationale)	School policy documents School handbooks School website content SLT survey Teacher survey Pupil survey	One time point
Individual factors (pupils): age, gender, ethnicity, socioeconomic position, eligibility for Free School Meals and whether pupils have English as an additional language and/or special educational needs	Pupil survey Teacher survey	One time point
Contextual factors: school, individual, family/home	Focus groups with school staff, pupils and parents/carers of school pupils	One time point
Economic variables		
Teacher time spent managing policy Indirect time spent managing behavioural problems Other related costs	SLT survey Teacher survey	One time point
Health-related quality of life/quality adjusted life years	The Child Health Utility Instrument (CHU9D)^80^/pupil survey	One time point/current assessment

SLT, senior leadership team.

#### Pupil online survey

Pupils complete an online survey at one time point (in school time) that includes validated measures for mental well-being, anxiety and depressive symptoms, addictive social media use, motives for social media use, health-related quality of life and demographic variables (eg, age, gender) (table 3). Within the survey, pupils are asked to self-report data on their physical activity levels, sleep and phone/media use, and by using data from their iOS or Android apps, they additionally self-report data on time spent on their smartphone and social media apps (table 3). Within the survey, pupils are also asked to report on their knowledge and understanding of the school smartphone policy and compliance with the school smartphone policy. The survey is completed on encrypted tablets, using a portable Wi-Fi hub owned by the research team.

#### Secondary measure of mental well-being

A second online survey (in school time) to measure mental well-being (table 3) is completed 4–8 weeks after pupils have completed the initial online survey. The SLM is sent an email link for pupils to complete.

#### Teacher online survey

Data are collected from the form teacher (or an equivalent teacher responsible for the class) for each participating pupil on: pupil attainment; classroom behaviour; and whether pupils are eligible for free school meals, have a special educational need or have English as an additional language (table 3). Within the survey, teachers are also asked to report on their knowledge and understanding of the school smartphone policy, compliance with the school smartphone policy and to report on the time they spend implementing the school smartphone policy (table 3). Teachers are sent the online survey by email.

#### SLT online survey

The SLT member responsible for the school smartphone policy is asked to complete survey questions on the SLT member’s role; the school timetable and school policies; features of the school smartphone policy; perceived time spent by school staff developing and implementing the school smartphone policy; knowledge and understanding of the school smartphone policy; and compliance with the school smartphone policy. The SLT member is sent the online survey by email.

#### Accelerometers

Pupils are asked to wear a wrist worn GENEActiv accelerometer watch for 24 hours a day for the subsequent 7 days after completing the survey.^64^ Watches are worn on the non-dominant wrist during all activities, including water-based activities. Accelerometers are initialised to collect data in 100 Hz. Data will be analysed in R to produce physical activity and sleep outcomes (table 3).

#### Document analysis

School policy documents and handbooks related to smartphones, social media, pupil behaviour, mental health/well-being, e-safety/IT policy and the wider school aims and ethos are collected. Documents related to the school timetable are also collected so that time spent in physical education, and time allocated for breaks and lunch can be quantified for each school.

### Case study schools

Six case study schools are being purposively sampled from the 30 participating schools in relation to two school characteristics: (1) smartphone policy type and duration to ensure a balance of restrictive (n=3) versus permissive policies (n=3), and a range of length of policy implementation in the six case studies; and (2) schools from low, medium and high area of deprivation, measured by the IDACI. An additional £300 compensation is allocated to case study schools.

Across the case study schools, up to 36 focus groups (FGs) will be completed with adolescents (n=12), school staff (n=12) and parents/carers (n=12). Data collection is taking place following the school level data collection (ie, surveys, accelerometers and document analysis) and following obtaining written consent (or assent). In each case study school four to six FGs are completed: adolescents (n=2), school staff (n=1–2) and parents/carers (n=1–2). Each FG comprises four to six members and aims to balance gender and ethnicity (where possible). For adolescents, one FG is completed with year 8 (age 12–13) and one with year 10 (age 14–15) pupils. School staff FGs include SLT, school governors, teachers and support staff (admin, caretakers, teaching assistants). Parents/carers of pupils from within the school (excluding sixth form, age 16–19) are recruited.

FGs are led by research staff employing established elicitation and semistructured interview techniques.^65 66^ Each FG lasts approximately 60 min and takes place in school or online. Data are collected from voice transcription.

